### Study setting

The study will be conducted in a UK tertiary academic referral centre specialised in kidney cancer care.

### Eligibility criteria

The inclusion criteria for entry in cohort include adult (≥18 years of age) of any gender participants capable and who have provided informed consent and that have been diagnosed with a SRM (≤4 cm of largest axis on cross-sectional imaging). Exclusion criteria include inability to provide informed consent and advanced disease (N1 and/or M1 on TNM staging).

The inclusion criteria for the embedded RCT include, in addition to the above-mentioned criteria, biopsy-proven RCC and equal feasibility for treatment with either percutaneous cryoablation or partial nephrectomy. Exclusion criteria include any concurrent medical/surgical condition or indication, which would mean the specialist multidisciplinary team (SMDT) meeting recommends one treatment modality is more suitable than another, such as:Myocardial Infarction in preceding 6 months.Pulmonary disease not allowing for prolonged anaesthesia.Multiple previous abdominal surgery/interventions, making surgical approach high risk.Performance status ≥2.Metastatic disease.Charlson comorbidity index >3.Patients with multifocal tumours.Patients with suspected or diagnosed with inherited kidney cancer susceptibility syndromes.Women that are pregnant or breast feeding (this is due to the fact that percutaneous cryoablation is done under CT guidance with associated radiation exposure).

Eligible patients will be identified at the weekly renal SMDT meeting by the chief investigator or a member of the clinical research team. All participants who wish to enter the study will be fully screened and consented by the Chief Investigator, one of the qualified clinicians involved in the study as Clinical Co-Investigator, or senior study staff when counter signed by a delegated clinician.

### Interventions

Cohort participants eligible for the embedded RCT will be randomised 1:1 and invited to consider the trial intervention (percutaneous cryoablation). Randomisation will be performed in blocks of 10 participants through the online system ’Sealed Envelope' (www.sealedenvelope.com) to ensure allocation concealment. This will be an open label trial with unblinded outcome assessment.

The control group will be composed of participants treated with standard of care (partial nephrectomy). The trial intervention will be performed by interventional radiologists under CT guidance using argon probes to freeze and kill the tumour. The standard of care will be performed by urological surgeons with da Vinci robot assistance.

No restrictions will be placed on other clinically necessary concomitant care. Follow-up for the purposes of this feasibility trial will be 6 months, but standard clinical follow-up will be at least 5 years (table 1—visit schedule and assessments). On average, patients attend two clinic appointments prior to treatment. Post-treatment follow-up is based on histological findings at biopsy/surgery but usually involves 6 monthly clinic visits for a minimum of 5 years. Participants will not be required to have any additional visits, apart from volunteers for focus groups and structured interviews.

**Table 1 T1:** Visit schedule and assessments

Procedures	Visits								
	Screening	Baseline	Intervention	Week 4 post-intervention (only second stage of study)	Month 6 after baseline (first stage of study) or intervention (second stage of study)	Y1	Y2	Y3	Y5
Demographics		X							
Medical history		X							
Physical examination		X		X					
Consent		X	X						
Blood test		X		X	X	X	X	X	X
Imaging	X				X	X	X	X	X
Questionnaire		X		X	X	X	X	X	X
Cryoablation or partial nephrectomy			X						
Case report form		X	X	X	X	X	X	X	X
Adverse event reporting		X	X	X	X	X	X	X	X
Biobanking of blood/urine/tissue		X	X	X	X	X	X	X	X

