### Study design

Single-centre prospective feasibility cohort study of adults that have been diagnosed with a SRM (n=200) with an open label embedded interventional RCT comparing nephron sparing techniques (figure 1 – Trial flow chart).

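### A single published block size of 10 in a one-centre, open-label trial makes some allocations predictable to the team that judges eligibility, so the online system alone does not secure concealment

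*Protocol article*

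**What the plan says.** All references are to the protocol article.

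- **Interventions**, ratio: "Cohort participants eligible for the embedded RCT will be randomised 1:1 and invited to consider the trial intervention (percutaneous cryoablation").
- **Interventions**, method: "Randomisation will be performed in blocks of 10 participants", through a named web service, with the stated purpose "to ensure allocation concealment". One block size is given. Nothing says that it varies or is kept from the recruiting team, and no stratification is mentioned.
- **Interventions**, blinding: "This will be an open label trial with unblinded outcome assessment".
- **Study design**: "Single-centre prospective feasibility cohort study of adults", so one sequence serves one team.
- **Eligibility criteria**: "Eligible patients will be identified at the weekly renal SMDT meeting", by the chief investigator or the clinical research team. Entry to the embedded trial requires biopsy-proven carcinoma and "equal feasibility for treatment with either percutaneous cryoablation or partial nephrectomy". The list of exclusions is introduced as examples of reasons why the meeting might prefer one modality.
- **Study design**: those selected are invited to cryoablation and asked for a second consent. Those not selected go to partial nephrectomy with no second trial consent.

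**The concern.** Concealing a list and making it unpredictable are different things. A web service does the first. It cannot stop a team that sees every past allocation from counting how many places each arm has left in a block of known size. Here each allocation reveals itself, because the patient either is invited to cryoablation or proceeds to surgery.

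The people able to count also decide, before randomisation, whether the next patient is equally suited to both treatments. Someone expecting a particular arm next could judge a borderline patient differently or defer entry. As a hypothetical example, a complex tumour might be held back when cryoablation is expected. The article's Introduction itself names professional resistance, from a perceived lack of equipoise, as an obstacle to surgical trials.

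Two results could be affected. The arms might no longer be comparable. The consent rate, asked only of those selected, might no longer come from a random half of eligible patients. The consent rate bears on the primary outcome (recruitment). Under Sample size and recruitment, both the consent rate and the comparison of complications between arms are triggers at the 12-month interim analysis, which can lead to stopping.

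**Working it through.** The article gives no figure for predictability, so there is none to reproduce.

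**Inputs.** Block size 2m = 10, so m = 5 per arm (Interventions). Ratio 1:1 (Interventions). Target 50 participants, which is five blocks if 50 are randomised (Sample size and recruitment). Assumptions: the size is always 10, there is one unstratified sequence, and the observer knows all earlier allocations.

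**Allocations certain in advance.** Once one arm's places in a block are used up, the rest of the block is known. The m allocations to one arm fall at random into the m + 1 gaps formed by the other arm's m allocations, so on average m/(m + 1) of them lie in the last gap. Adding both arms gives:

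2m/(m + 1) = 10/6 = 1.67 per block, or 16.7%.

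Over five blocks: 5 × 1.67 = 8.3 of 50. The last allocation in every block is always known.

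**Best guess.** The observer always guesses the arm with more places left. Expected correct guesses per block:

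m + 2^(2m−1)/C(2m, m) − 1/2 = 5 + 512/252 − 0.5 = 6.53.

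That is 65.3%, or 5 × 6.53 = 32.7 of 50, against 25 of 50 by chance. Exact enumeration of the block gives the same values. It also shows that in 38.7% of positions the next arm can be called with probability of at least 2/3.

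**If more than 50 are randomised.** Randomisation precedes the second consent. If 50/0.30 ≈ 167 eligible patients were randomised, about 167 × 0.1667 ≈ 28 allocations would be certain. The share is unchanged.

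**Comparison with a smaller fixed block.** A block of 4 gives 33% certain and 71% guessed correctly, so 10 is better than a small fixed block.

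**Effect of varying the size.** The article gives no alternative sizes, so these sets are assumed. Simulation of 3,000 lists of 50, with an observer who knows the set of sizes but not their order:

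| Block sizes | Certain per 50 | Best guess right |
|---|---|---|
| 10 only | 8.3 | 65% |
| 6, 8, 10 | 0.9 | 66% |
| 4, 6, 8 | 1.2 | 68% |
| 4, 6, 8, 10 | 0.6 | 67% |

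Varying the size removes most of the certain calls but does not lower best-guess success.

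**What withholding adds.** A separate simulation used an observer who bets only on the arm that is behind overall, without using the sizes. This also scored 66% with 6, 8 and 10. Withholding the sizes therefore takes away certainty and the knowledge of how strong a guess is. It does not defeat a crude bet on the lagging arm by someone who knows that allocation is kept balanced.

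**The case against.** **Predictability is partial.** About five allocations in six are not certain, and a block of 10 is less predictable than smaller ones. This stands, and it limits the size of the point.

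**Entry is not a free judgement.** Biopsy proof is required, explicit exclusions are listed, and suitability is tied to a multidisciplinary recommendation. Candidates are already consented cohort members with comorbidity, performance status and tumour complexity recorded at baseline, so a withheld patient would leave a trace. This limits selection and makes it checkable, but equal suitability remains a judgement made before allocation.

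**The consequence is modest.** The outcome is feasibility, Statistical methods calls all analyses exploratory, and no confirmatory comparison depends on the sequence. This stands.

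**Some premises rest on a condensed article.** A fixed size is inferred from the single size given, and the absence of stratification from silence. The full protocol might differ. That staff know every earlier allocation is likely at one open-label centre but is not stated. The published size and the concealment claim, however, are stated.

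**Stronger readings.** A reader might infer that the comparison or the consent rate is biased. The article does not show that. Bias would require staff to count and to act on the count, and its size cannot be estimated from what is given. A reader might also take the block sentence to mean that patients wait until ten have accrued, which would delay treatment. Nothing in the article says that anyone is held, and ordinary permuted blocks are the natural reading. A delay based on 25 a year (10/25 × 12 = 4.8 months) would also use the recruited rate, whereas it is eligible patients who are randomised. At 25/0.30 ≈ 83 a year it would be 1.4 months. No delay is claimed here.

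**Conclusion.** The concern holds in a limited form. With a known block of 10 at 1:1, about 8 of 50 allocations are certain in advance and the best guess succeeds about 65% of the time. The claim that the online system ensures concealment is therefore stronger than the design supports. This rests on the size being constant, the sequence unstratified, and earlier allocations visible to those who judge eligibility. Selective or delayed entry is possible but not shown. Given that and the exploratory purpose, this is a minor-to-moderate weakness that is cheap to correct.

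**What to change.** Amend Interventions to state that each participant is randomised individually, after eligibility for the embedded trial has been confirmed and recorded, in permuted blocks of randomly varying size. State also that the sizes are withheld from staff of the multidisciplinary meeting, from recruiting staff and from publications until recruitment ends.

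Both parts are needed. Varying the sizes cuts certain allocations from about 8 to about 1 per 50 (with 6, 8 and 10, assumed) but leaves best-guess success at about 66% if the set is known. Because 10 is already public, withholding helps only once the scheme has changed.

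The cost is a setting in the randomisation service, a one-sentence amendment and a possible final imbalance of a few patients. With a largest block of 10, stopping mid-block leaves the arms at most 5 apart, whereas five full blocks of 10 give 25 and 25.

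Some guessing remains under any blocked scheme. Only unblocked allocation would bring it to 50%, at the price of a larger possible imbalance: for 50 participants the difference between arms would have a standard deviation of √50 ≈ 7. That trade is not needed for a feasibility study.

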### Sample size and recruitment

The aim of this study is to assess the feasibility of a large definitive trial comparing partial nephrectomy and percutaneous cryoablation in the treatment of SRM and to inform the design, sample size and outcome measures for a subsequent large multicentre prospective trial, so formal sample size calculations are inappropriate. We will aim to recruit 50 patients into the embedded randomised study, randomised equally between the two groups. This sample size will allow the assessment of whether the consent rate of 30% has been achieved with a 95% CI of ±11%. Sample sizes between 24 and 50 have been recommended to estimate the SD required for sample size calculation to allow design of a full trial.^20 21^ We anticipate being able to recruit at least 30% of eligible patients which equates to 25 patients annually, and a total recruitment time of 24 months.

Recruitment issues will be pre-empted and identified early by the qualitative researcher and their team, ensuring successful delivery of both the initial feasibility trial and full trial. This will include participant involvement in semistructured interviews and focus groups to explore views on the presentation of the study information, understanding of the trial process and reasons underlying decisions to accept or decline the trial. As part of the qualitative research effort, participants who volunteer to take part in structured interviews and focus groups will be asked to participate in additional visits. Trial management group members and clinician involvement will also take part in semistructured interviews to explore their perspectives on the study design, and their experiences with recruitment.

If interim analysis after 12 months of initiation of recruitment shows evidence of any of the following:consent rate of <30%,cryoablation results in more than a 50% increase in complications compared with partial nephrectomy at 90 days,the intervention results in more than a 50% increase in waiting time for treatment compared with the standard treatment group, then a detailed ‘plan of action’ will be formulated together with the qualitative research team to identify any areas in the recruitment/study pathway that can be improved. A detailed report will be presented to the Sponsor, Trial Steering Committee and the Data Monitoring Committee. If no remedial actions are deemed suitable, then the trial will be stopped.

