**Figure 1 F1:**
[figure not shown]
Study flow chart.

This pragmatic study design incorporates a two-stage consent process:The first stage allows the creation of a prospective observational cohort of patients with SRMs. Cohort participants will be managed at patient and clinicians’ discretion and consent for: (a) long-term follow-up and data linkage to NHS digital and/or other central NHS registries; (b) future randomised invitation for new interventions, tests, or treatments; (c) participation in interventional trials as a control group without need of further consent; (d) PROMs/questionnaires completion; and (e) biobanking of blood/urine/tissue.In the second stage, cohort participants with biopsy-proven renal cell carcinoma (RCC) who are eligible for both percutaneous cryoablation and partial nephrectomy will be randomly selected (1:1) and invited to consider percutaneous cryoablation (n=25). Participants randomly selected to consider the trial intervention (percutaneous cryoablation) will be asked for informed consent (second consent process) and will form the interventional arm. Participants not randomly selected to consider the trial intervention will receive standard of care (partial nephrectomy) and will form the control arm. By virtue of having agreed to be part of control trial arms at the first stage consent process, these participants will not require a second consent process. They will, however, be subject to surgical consent for the procedure as part of standard practice.

Patient information sheets and consents forms are available in online supplementary document 2 to 5.

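### The stated 95% CI of ±11% for a 30% consent rate does not follow from 50 patients (±12.7 points), and the denominator of the consent rate is not defined

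*Protocol article*

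**What the plan says.** All references are to the protocol article.

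- Sample size and recruitment sets the target: "We will aim to recruit 50 patients into the embedded randomised study, randomised equally between the two groups". The next sentence attaches a precision to it: "This sample size will allow the assessment of whether the consent rate of 30% has been achieved with a 95% CI of ±11" (per cent).
- The same section then cites a recommended range of 24 to 50 patients for estimating a standard deviation. It also expects to recruit at least 30% of eligible patients, which it equates to 25 a year over 24 months.
- Study design (two-stage consent, after Figure 1) says that eligible cohort members "will be randomly selected (1:1) and invited to consider percutaneous cryoablation (n=25"). The Abstract attaches the same number to the same group. On consent it says: "Participants randomly selected to consider the trial intervention (percutaneous cryoablation) will be asked for informed consent (second consent process"). Of the controls it says that "these participants will not require a second consent process".
- Objectives and outcomes makes feasibility of recruitment the primary outcome. A consent rate below 30% at the 12-month interim analysis is one of three triggers for a plan of action.

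The article gives no formula for the interval, no correction and no definition of the consent-rate denominator.

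**The concern.** There are two separate problems. First, the words tie the precision to the sample of 50, and ±11 looks too narrow for a 30% proportion in 50 people. Second, 50 may not be the right denominator. In this design the control half of the trial makes no second-stage decision to accept or decline, so a consent rate for cryoablation can come only from those offered it. Yet the same section applies 30% to eligible patients, a different and larger group.

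At stake is how the primary outcome will be read. Someone told ±11 will take an observed 30% to mean roughly 19% to 41%. Whether that is too optimistic or too cautious cannot be judged until the denominator is known.

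**Working it through.** **Inputs.** Rate p = 0.30, 95% confidence, stated half-width 0.11 and n = 50 (Sample size and recruitment); 25 invited (Abstract, Study design); cohort of 200 (Study design). Two further denominators are implied but not stated: 25/0.30 = 83.3 eligible a year, and 50/0.30 = 166.7 eligible over 24 months. The figure of 83 also arises if 25 is the number who accept rather than the number invited.

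**Step 1: try to reproduce the stated figure.** The normal-approximation (Wald) half-width is 1.96 × √(p(1−p)/n). At n = 50 this is 1.96 × √(0.21/50) = 1.96 × 0.0648 = 0.127, or ±12.7 points. Other 95% methods for 15 of 50:

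| Method | Interval | Half-width (points) |
|---|---|---|
| Wilson | 19.1% to 43.8% | 12.3 |
| Agresti-Coull | 19.0% to 43.8% | 12.4 |
| Jeffreys | 18.7% to 43.6% | 12.4 |
| Clopper-Pearson | 17.9% to 44.6% | 13.4 |
| Wald with continuity correction | 30% ± 13.7 | 13.7 |

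None gives 11.

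**Step 2: the n that would give ±11.** n = 0.21 × (1.96/0.11)² = 66.7, so about 67. If 11 is a rounded figure, half-widths of 11.5 and 10.5 correspond to n of about 61 and 73. Neither end reaches 50.

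**Step 3: the other denominators in the text (Wald, p = 0.30).**

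| Denominator | n | 95% half-width (points) |
|---|---|---|
| Invited to consider cryoablation | 25 | 18.0 |
| Total in embedded trial | 50 | 12.7 |
| Eligible per year, or offered if 25 accept | 83 | 9.9 |
| Eligible over 24 months | 167 | 7.0 |
| Whole cohort | 200 | 6.4 |

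None gives 11. At n = 25 the exact interval is visibly asymmetric. Clopper-Pearson evaluated at 30% is about 13.5% to 51.5%. The nearest observable results are 7 of 25 (about 12% to 49%) and 8 of 25 (about 15% to 54%).

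**Step 4: what does come near 11 at n = 50.** Each route changes a stated term or adds an unstated one.

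- A 90% multiplier: 1.645 × 0.0648 = 10.7 points.
- A finite-population correction against the cohort of 200: 12.70 × √(150/199) = 11.0 points. Against 167 it is 12.70 × √(117/166) = 10.7 points.
- A rate of 20% instead of 30%: 1.96 × √(0.16/50) = 11.1 points.

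**The case against.** The best defence of the number is the finite-population correction, which gives ±11.0 with the cohort of 200. It does not rescue the sentence. The correction is not mentioned, the 200 are everyone with a small renal mass rather than those eligible for the trial, and such a correction does not suit a study meant to inform a later multicentre trial. A 90% interval contradicts the stated 95%.

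The best defence against the ±18 figure is stronger. A reader might infer that the true interval is the one from 25 people, about 1.6 times as wide as stated (18.0/11). The two-stage consent text supports 25 well, but other text pulls the other way. The sample size section speaks of recruiting 50 and applies 30% to eligible patients. If only 25 were asked and 30% accepted, just 7 or 8 would have consented to cryoablation, which sits awkwardly with recruiting 50. On the eligible-patient readings the precision is better than ±11. So ±18 is one well-supported reading, not an established fact.

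Two further inferences also go too far. One is that the choice of 50 rests on ±11 alone; the same section also cites 24 to 50 patients for estimating a standard deviation and calls formal calculations inappropriate. The other is that the 12-month rule inherits the error; that rule compares the consent rate with 30% and does not use the ±11. It leads first to a plan of action, and to stopping only if no remedy is found suitable.

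The feasibility label and the exploratory status of the analyses (Statistical methods) limit the consequences, but they do not make a published figure correct.

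**Conclusion.** The precision statement is wrong as written. For the 50 patients it refers to, the 95% half-width at 30% is ±12.7 points by normal approximation and 12.3 to 13.7 across the methods tried. A half-width of ±11 corresponds to about 67 people, a number that appears nowhere in the article.

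The consent-rate denominator is also undefined. The candidates in the text give half-widths from ±18.0 (25 invited) to ±7.0 (167 eligible). The size and direction of the error therefore depend on which is meant, but no candidate yields ±11. These figures assume a true rate of exactly 30%, independent decisions and a two-sided interval. The counts 83 and 167 are derived from the article's recruitment expectation and are not stated in it.

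How ±11 arose cannot be determined from the article, since several unstated changes come close to it.

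**What to change.** Define the consent rate in Sample size and recruitment, then replace ±11% with the 95% interval for that denominator and name the method. For example:

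> The consent rate is the number accepting cryoablation divided by the number offered it. With 25 offered and a rate of 30%, the 95% CI is about ±18 percentage points (normal approximation).

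If an exact method is preferred, quote its two limits (Clopper-Pearson, about 13.5% to 51.5%) rather than a ± figure. If another denominator is intended, name it and give its half-width: 50, ±12.7; 83, ±9.9; 167, ±7.0. Use the same definition for the primary outcome and for the 12-month check against 30%, and say whether 25 is the number offered cryoablation or the number who accept it.

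The cost is one or two sentences, with no extra patients and no change to conduct. With 25 or 50 as denominator, the stated precision becomes less favourable; with 83 or 167 it improves.

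### One 30% consent rate drives accrual, precision and the interim trigger, but it is not matched to a design that randomises before it invites

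*Protocol article*

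**What the plan says.** Three uses of a 30% rate stand in Sample size and recruitment of the protocol article.

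- Accrual: "We anticipate being able to recruit at least 30% of eligible patients which equates to 25 patients annually", with "a total recruitment time of 24 months".
- Size and precision: "We will aim to recruit 50 patients into the embedded randomised study, randomised equally between the two groups", followed by "This sample size will allow the assessment of whether the consent rate of 30% has been achieved with a 95% CI of ±11" per cent.
- Interim: "If interim analysis after 12 months of initiation of recruitment shows evidence of any of the following", the first listed item being a consent rate below 30%. Any listed item leads to a plan of action, and to stopping if no remedy is judged suitable.

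The order of events is set elsewhere. Interventions says: "Cohort participants eligible for the embedded RCT will be randomised 1:1 and invited to consider the trial intervention (percutaneous cryoablation"). Study design (text under Figure 1) attaches n=25 to those invited to consider cryoablation and asks only them for a second consent. Of those not selected, who become controls, it says that "these participants will not require a second consent process".

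The article does not give the numerator or denominator of the consent rate.

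**The concern.** The accrual line reads like that of a conventional trial, in which all eligible patients are asked, 30% agree and those who agree are randomised. Here there are two consents at different points. Broad first-stage consent admits a patient to the cohort. Randomisation follows, and second-stage consent is then sought from the invited half only. A 30% rate at the first step limits how many are randomised and says nothing about who accepts cryoablation. A 30% rate at the second step does the opposite. One undefined 30% cannot serve the accrual projection, the precision statement and the interim trigger together.

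Feasibility of recruitment is the primary outcome, and the article says that success would enable a larger multicentre trial. The rate is therefore both the main result and a threshold that can lead to stopping. If it is read as cohort entry, the study could pass its own test while most of those invited decline cryoablation.

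**Working it through.** **Inputs** (all from the article): 30%; 25 a year; 24 months; 50 randomised 1:1; 25 invited; 95% CI of ±11%; interim at 12 months; cohort n=200. The number eligible per year is not stated, so it is back-calculated.

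**The plan's own figure.** Implied eligible per year = 25 / 0.30 = 83.3. Over 24 months this is 83.3 × 2 = 166.7, and 166.7 × 0.30 = 50. The stated total is reproduced, provided that the 30% acts before randomisation.

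**Precision.** The 95% half-width is 1.96 × √(0.30 × 0.70 / n):

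| n | What n would be | Half-width |
|---|---|---|
| 12.5 | invited by month 12, at 25 randomised a year | ±25.4% |
| 25 | all invited | ±18.0% |
| 50 | all randomised | ±12.7% |
| 166.7 | all eligible over 24 months | ±7.0% |

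A half-width of 11% needs n = 1.96² × 0.21 / 0.11² ≈ 67, which is the size of no group in the plan.

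**Reading A: the 30% is second-stage consent, and the 83.3 a year are eligible cohort members.** All of them are randomised.
- Time to 50 randomised: 50 / 83.3 × 12 = 7.2 months, not 24, and about 5 months before the interim look.
- Acceptors among 25 invited: 25 × 0.30 = 7.5, with the rate known to ±18.0%.
- If n=25 is taken to mean acceptors instead, 25 / 0.30 = 83.3 must be invited and about 167 randomised. That takes 167 / 83.3 ≈ 2 years, so 24 months and a mid-course look fit. The sizes do not: there would be 83 controls against 25, and 167 / 200 = 83% of the cohort would have to be eligible for the RCT.

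**Reading B: the 30% is entry of eligible patients into the cohort.**
- Randomised per year: 83.3 × 0.30 = 25, so 50 in 24 months, with the 12-month look at half accrual. Size, duration and timing fit.
- The rate's denominator is 166.7, so its precision is ±7.0%, not ±11%.
- Invited per year: 25 / 2 = 12.5. Nothing is assumed about how many accept. If 30% did, that would be 12.5 × 0.30 = 3.75 a year, or 7.5 in 24 months.
- A consent trigger on cohort entry would not register refusals of cryoablation.

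**The case against.** The strongest reply is that the figures have a consistent reading. Eligibility criteria uses the term eligible patients for people found at the weekly multidisciplinary meeting, before any consent. Interventions uses a different expression for the group that is randomised, namely cohort participants eligible for the RCT. If the two are kept apart, Reading B follows, and the 50 would be 50 / 200 = 25% of the cohort, which is plausible given the biopsy and equal-suitability criteria. This stands. A reader might infer that 30%, 25 a year, 50 and 24 months cannot all hold; the article does not support that.

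A reader might also infer that about 167 must be randomised to obtain 25 acceptors. The article does not support that either. It attaches 25 to those invited, counts 50 as randomised, plans an intention-to-treat analysis and nowhere clearly makes 25 acceptors the stopping count.

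Nor would the 12-month look be useless under Reading A. It also covers complications and waiting time, the qualitative work is meant to find problems earlier, and lessons carry over to the full trial.

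Finally, this is a condensed article on an exploratory study, and the full protocol may define the rate. That would excuse silence on detail. It does not reconcile the stated figures: Reading B leaves the ±11% unexplained and leaves acceptance of cryoablation outside both the projection and the trigger.

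**Conclusion.** The point holds as a mismatch between one undefined rate and a two-consent design, not as an arithmetic impossibility. Neither reading serves all three uses of the 30%. As second-stage consent, it cannot limit the number randomised: 50 are reached in about 7 months, and the 25 invited yield about 7.5 acceptors, known to about ±18%. As cohort entry, it supports 25 a year, 50 and 24 months, but its precision is about ±7%, and the step that decides whether the embedded RCT is feasible goes unmeasured by the stated criterion.

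These sizes rest on two assumptions: that 83 eligible a year, implied by 25 / 0.30, is what the authors had in mind, and that 30% is the acceptance rate among those invited wherever acceptors are counted. Because the rate bears on the primary outcome and can lead to stopping, it should be settled before the interim look.

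**What to change.** In Sample size and recruitment, replace the single rate with two:

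1. The proportion of eligible patients who enter the cohort, with its denominator, used for the accrual projection only.
2. Acceptance among those invited to cryoablation (acceptors / invited), used for the feasibility criterion and the interim trigger of below 30%.

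Then:
- Give the expected numbers eligible, randomised, invited and accepting per year. With 25 invited, expect about 7 to 8 acceptors at 30%.
- Restate the precision on the invited denominator: about ±18% at 25, in place of ±11%.
- Say which count ends recruitment.
- Tie the interim consent check to a number of answered invitations rather than to month 12 alone. At 25 randomised a year, only about 12 or 13 would have been invited by then.

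The cost is a rewrite of one paragraph. The downside is that the stated precision and the expected number treated with cryoablation look less favourable. No increase in the randomised total is required.
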